| 
Procedures: Visits at days 7, 21, 14, 28, 90 and 365.
                                                                                                                                                                                                                                                                                                                                                                                                                                                                                                                                                                                                                |
| 
Duration of treatment = 2 hours, duration of surveillance per patient = 365 days
                                                                                                                                                                                                                                                                                                                                                                                                                                                                                                                                                                                     |
| 
Statistical Considerations: Intention to treat analysis, expected mortality at day 28 = 40%, expected relative reduction with study intervention = 30 %, <math>\alpha</math> = 5%, <math>\beta</math> = 20%, number of subject to include = 500. Interim analyses at 100, 200, 300 and 400 patients included.
                                                                                                                                                                                                                                                                                                                                                        |

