### 9.2. Description of population

- The study population will be patients with SARS-CoV-2 pneumonia associated with acute respiratory failure and requiring mechanical ventilation
- Number of patients planned: 500 (1 intervention group of 250; 1 control group of 250)

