## 9.9. Statistical Analysis

- Primary outcome

The primary outcome of the trial is mortality at day 28. Based on prior reports from China, Italy and UK, and consistent with personal observations, we anticipate that the mortality at day 28 will be around 40 %. As no comparative study has yet been published, the reduction that we anticipate is empiric. We consider that a one third relative reduction in 28-day mortality is realistic and clinically relevant. As this reduction might be greater, we plan to perform an interim analysis for ethical reasons. With a two-sided  $\alpha$ -risk of 0.05 and a  $\beta$ -risk of 0.20, the minimal number of patients to include to reach significance for a one third relative reduction in 28-day mortality (an absolute reduction of 13.5% day-28 mortality in the intervention group assuming a day-28 mortality of 40 % in the control group) is 250 in the control group and 250 in the active group (total number of patients = 500). This number allows for four interim analyses to be performed in addition to the final analysis, respectively after assessment of 100, 200, 300, 400 and 500 patients. Considering that others trials in COVID-19 may result in modification in mortality and therefore in standard of care, we anticipate that the number of patients that is necessary to address our hypothesis may vary, and will have to be adapted depending on the results of the interim analyses.

- Statistical analysis plan

Results will be analysed in intention to treat and expressed as means and standard deviations (SD) for quantitative variables with a Normal distribution and as medians and 25th to 75th percentiles for skewed distributed quantitative variables. Qualitative variables will be expressed using counts and percentages.

Mean values between groups will be compared by Student t-test but also by the non-parametric Wilcoxon test when normality assumption is not fulfilled. Proportions will be compared by the chi-square

test. Appropriate multivariate analyses will be performed to assess the relationship between outcome and patients' characteristics and clinical features.

For the primary endpoints, vital status at day 28 in all groups will be calculated with corresponding 95% CI. Comparison between groups will be tested using chi-square test.

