Regarding the secondary endpoints, quantitative values between groups will be compared by Student t-test or non-parametric Wilcoxon for the SOFA score (at different time points), viral load of SARS-CoV-2 (at different time points), circulating CRP (at different time points), ADL score at day 90, anxiety-depression scale at day 90, sero-conversion. Poisson regression analysis will be considered to analyse number of ventilator-free days up to day 28. Comparison of proportions will be applied to compare location of patient at day 90, as well as presence of various adverse events. If descriptive analysis revealed the presence of potential confounding factors, appropriate multivariate analysis will then be considered.

The two-sided level of significance used in this trial is 5%. Statistical analyses will be carried out using SAS (version 9.4 for Windows) statistical package.

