#### – Interim analysis plan

Due to ethical considerations of the current situation, we propose to conduct a group-sequential design with several interim analyses. The objective of including interim analyses in the study design is to allow the possibility of stopping the study early if a clinically relevant benefit is already established from a statistical point of view. Conversely, the interim analyses also allow the possibility of an early stopping of the study if the observed benefit, at the time of the interim analysis, is so small as to make it extremely unlikely that the study would succeed, were it continued until full accrual. Finally, the interim analyses will also include a futility stopping rule for the SOC group, which may appear to be unjustified if mortality in that group appears too large to be acceptable.

Specifically, the interim assessment of the SOC group will be based on the numbers of patients and of deaths shown in Table 1. The recommendation will be made to stop accruing patients in the SOC group if the number of deaths observed in this group suggests a true mortality rate in excess of 0.4. The rule for DSMB recommendation shown in Table 1 will not be binding.

**Table 1:** interim analysis and potential recommendation of the DSMB to stop the SOC group

| Interim analysis | Number of patients in SOC group | Recommend to stop SOC group if number of deaths | Probability of seeing this number of deaths if true mortality rate $\leq 0.4$ |
|------------------|---------------------------------|-------------------------------------------------|-------------------------------------------------------------------------------|
| 1                | 25                              | $\geq 14$                                       | $< 0.034$                                                                     |

|   |     |           |           |
|---|-----|-----------|-----------|
| 2 | 50  | $\geq 26$ | $< 0.031$ |
| 3 | 75  | $\geq 37$ | $< 0.04$  |
| 4 | 100 | $\geq 48$ | $< 0.042$ |

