The interim analyses will be performed with 100, 200, 300 and 400 patients evaluable for 28-day mortality. Two Lan-Demets spending functions will be used: one, similar to a Pocock (aggressive) boundary to stop the study for futility, and the other, similar to an O'Brien-Fleming (conservative) boundary to stop the study for extreme efficacy. If the interim analyses take place with increments of exactly 100 patients, and assuming a mortality of 40% in the control group, the recommendations to stop the study for futility or for efficacy are summarized in Table 2. Of note, the trial will reach statistical significance if the absolute difference in 28-day mortality is 9% or larger, which might still be a clinically worthwhile difference. The rules for DSMB recommendations shown in Table 2 will not be binding.

**Table 2:** interim analyses and potential recommendations of the DSMB to stop the trial for futility or efficacy, depending on the observed treatment effect (and associated P-value)

| Interim analysis | Number of patients | Recommend stopping for futility if difference in mortality is smaller than | Recommend stopping for efficacy if difference in mortality is greater than |
|------------------|--------------------|----------------------------------------------------------------------------|----------------------------------------------------------------------------|
| 1                | 100                | 0.02 ( $P > 0.83$ )                                                        | -                                                                          |
| 2                | 200                | 0.04 ( $P > 0.60$ )                                                        | 0.22 ( $P < 0.001$ )                                                       |
| 3                | 300                | 0.06 ( $P > 0.28$ )                                                        | 0.14 ( $P < 0.007$ )                                                       |
| 4                | 400                | 0.08 ( $P > 0.12$ )                                                        | 0.11 ( $P < 0.022$ )                                                       |
| 5 (final)        | 500                | -                                                                          | 0.09 ( $P < 0.042$ )                                                       |

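### The synopsis and section 9.9 attach the same 80% power and 500 patients to two different effects, and for the synopsis effect that power falls to about 67–69% if the Table 2 futility limits are followed

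*Protocol*

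**What the plan says.** The synopsis, under Statistical Considerations, gives "expected mortality at day 28 = 40%, expected relative reduction with study intervention = 30" per cent, with alpha 5%, beta 20% and "number of subject to include = 500". The same entry lists interim analyses at 100, 200, 300 and 400 patients.

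Section 9.9, under Primary outcome, keeps the two-sided alpha of 0.05, the beta of 0.20 and the total of 500, but plans for a relative reduction of one third, glossed as "an absolute reduction of 13.5% day-28 mortality in the intervention group assuming a day-28 mortality of 40 % in the control group".

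Section 9.2 fixes the split: "Number of patients planned: 500 (1 intervention group of 250; 1 control group of 250").

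The interim analysis plan in 9.9 states: "The interim analyses will be performed with 100, 200, 300 and 400 patients evaluable for 28-day mortality". It uses an aggressive, Pocock-like futility boundary and a conservative, O'Brien-Fleming-like efficacy boundary.

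- **Futility (Table 2):** stopping is recommended if the difference is below 0.02, 0.04, 0.06 and 0.08 at looks 1 to 4.
- **Efficacy (Table 2):** the limits are P below 0.001, 0.007 and 0.022 at looks 2 to 4, and below 0.042 at the final analysis.
- **Status:** the Table 2 recommendations are not binding.

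**The concern.** One sample size and one power cannot both belong to a 12-point effect and a 13.5-point effect under the same design. The synopsis mentions the interim analyses alongside the beta of 20%, so a reader will take 80% to be the power of the sequential trial. Futility limits that tighten from 0.02 to 0.08 remove some trials that would have gone on to succeed, and the protocol does not say how many.

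The ethics committee, the funder and the DSMB are therefore not told how likely the trial is to detect a true 30% reduction if the DSMB acts on the limits it is given.

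**Working it through.** **Inputs.** Control mortality 40% (synopsis and 9.9). Plasma mortality 28% (synopsis: 40% × 0.70), 26.7% (one third) or 26.5% (13.5 points). 250 per arm (9.2). Looks at 50, 100, 150, 200 and 250 per arm, with the limits of Table 2.

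**Step 1. The two effects.** 30% of 40% is 12 points. One third of 40% is 13.3 points. 13.5/40 = 33.75%.

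**Step 2. Reproduce the stated 500 as a fixed design.** With pooled variance under the null and no continuity correction,

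n per arm = [1.96·√(2·p̄·(1−p̄)) + 0.842·√(p₁(1−p₁) + p₂(1−p₂))]² / (p₁−p₂)²

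- 40% vs 28%: p̄ = 0.34, so n = (1.96 × 0.6699 + 0.842 × 0.6645)² / 0.0144 ≈ 244 per arm, 488 in total. Power at 250 per arm is 81.0%. The synopsis figure reproduces.
- 40% vs 26.5%: p̄ = 0.3325, so n = (1.96 × 0.6663 + 0.842 × 0.6594)² / 0.018225 ≈ 190 per arm, 380 in total. Power at 250 per arm is 89.6%. The 500 in section 9.9 does not reproduce as a fixed design.

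**Step 3. Power of the five-look design.** Each setting was simulated with 1,000,000 trials. The futility limits were applied as the printed differences or as the printed P-values, and so were the efficacy limits.

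| Plasma mortality | Futility ignored, efficacy by P-values | Futility ignored, efficacy by differences | Followed: all differences | Followed: all P-values | Followed: futility by differences, efficacy by P-values |
|---|---|---|---|---|---|
| 28% (12 points) | 80.2% | 77.5% | 67.3% | 67.7% | 68.6% |
| 26.7% (13.3 points) | 88.1% | 85.9% | 76.6% | 76.8% | 77.7% |
| 26.5% (13.5 points) | 88.9% | 86.8% | 77.6% | 77.7% | 78.7% |

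Numerical integration of the normal model, using the efficacy P-values, gives 66–67% for 12 points and 76–77% for 13.5 points with futility followed. With futility ignored it gives 79.8% and 88.6%.

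**Step 4. Where the power goes.** At a true 12-point benefit, with futility read as differences, the proportions stopping for futility at looks 1 to 4 are about 12.1%, 4.7%, 4.5% and 6.3%, or 27.6% in total. Reading the limits as P-values gives 28.0%.

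The first look can be checked by hand. With 50 per arm the observed difference moves in steps of 0.02, so a value below 0.02 means zero or less. The standard error is √[(0.24 + 0.2016)/50] = 0.0940. With a half-step correction, (0.01 − 0.12)/0.0940 = −1.17, which has probability 0.121.

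**Step 5. The significance level.** Lan-DeMets O'Brien-Fleming-type spending of an overall two-sided 5%, with looks at 200, 300, 400 and 500, gives nominal P-values of 0.0008, 0.0074, 0.0220 and 0.0422. These match Table 2. The printed P-values together give an overall two-sided error of 4.96%.

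**The case against.** **The limits are non-binding.** The synopsis arithmetic is correct as a fixed-sample calculation, and it remains correct (about 80%) with the Table 2 efficacy P-values when no futility stop is made. This stands, and it makes the loss conditional on the DSMB acting on the limits. But non-binding status protects the type I error. It does not restore power when a recommendation is followed. The 67–69% is the literal reading, in which every limit is followed; partial adherence falls between that and 80%.

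**Sample size may be adapted.** Sections 9.9 and 9.10 foresee changing the number of patients after interim analyses. That does not make the two stated design effects agree, and it does not supply the missing power figure.

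Four stronger readings are tempting but are not supported:

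- A reader might infer that "The two-sided level of significance used in this trial is 5" per cent contradicts the final P of 0.042. It does not. The 0.042 is the nominal final level that an overall 5% design produces (step 5). An error of about 5.7% would arise only if the final test were run at 0.05 in disregard of Table 2.
- A reader might infer that the look-4 futility limit is miscalculated, because a difference of exactly 0.08 gives P = 0.096 rather than 0.12. Table 2 rounds differences to two decimals. A difference of 0.075 gives P = 0.119, which fits the printed pair.
- A reader might infer that an unsigned P-value tells the DSMB to continue when plasma does harm. The criterion in Table 2 is the difference, and the P-value is only attached to it. A harmful difference is below every futility limit.
- A reader might set the limits against the stated purpose of stopping when the benefit "is so small as to make it extremely unlikely that the study would succeed, were it continued until full accrual". That sentence describes purpose. The operating rules are in Table 2, are not binding, and the protocol itself calls the futility boundary aggressive.

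**Conclusion.** The point holds as an inconsistency in the design effect and an incomplete statement of power. The synopsis (12 points) and section 9.9 (one third, or 13.5 points) claim the same alpha, beta and sample size. The synopsis figure matches a design without futility stopping. The figure in 9.9 comes close to 80% only with futility stopping. If the Table 2 futility limits are followed, power is about 67–69% for the synopsis effect, against about 80% if they are not, a loss of roughly 12 points (80.2 − 68.6 = 11.6 on the most favourable reading). For 13.5 points the figures are about 78–79% and 89%.

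These results assume 40% control mortality, exactly 250 per arm, looks at exact multiples of 100 evaluable patients, and full adherence wherever the limits are described as followed. The ranges reflect whether the limits are read as rounded differences or as P-values. Using the rounded differences for efficacy as well lowers the no-futility figure for 12 points to about 77–78%. There is no defect in type I error control.

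**What to change.** 1. State one design effect in the synopsis and section 9.9, with relative and absolute figures that agree. For a control mortality of 40%, 30% goes with 12 points, one third with 13.3 points, and 13.5 points with 33.75%. The choice of effect is the sponsor's.
2. Next to the sample size, give the power of the Table 2 design for the chosen effect, with futility limits followed and not followed: about 68% and 80% for 12 points, or about 78% and 89% for 13.5 points. Say which of the two the stated beta refers to.
3. In the same edit, section 9.9 may add that 5% is the overall two-sided level and that the final chi-square test is judged at the nominal 0.042 of Table 2. This is a clarification only.

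The cost is a few sentences and a less favourable stated power. No boundary has to be recalculated and no patients are added.

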## 5. Study Glossary

| Abbreviation | Meaning                                                 |
|--------------|---------------------------------------------------------|
| ADE          | Antibody Dependent Enhancement                          |
| ADL          | Activity of Daily Living                                |
| AE           | Adverse Event                                           |
| ARDS         | Acute Respiratory Distress Syndrome                     |
| COVID-19     | Coronavirus Disease 2019                                |
| CRF          | Case Report Form                                        |
| CRP          | C-Reactive Protein                                      |
| EC           | Ethics Committee                                        |
| ECMO         | ExtraCorporel Membrane Oxygenation                      |
| FAMHP        | Federal Agency for Medicines and Health Products        |
| GCP          | Good Clinical Practice                                  |
| HFO          | High Flow Oxygen                                        |
| KCE          | Belgian Healthcare Knowledge Centre                     |
| ICH          | International Conference on Harmonization               |
| ICU          | Intensive Care Unit                                     |
| IgG          | Immunoglobulin type G                                   |
| IVIG         | Intravenous Immunoglobulin Therapy                      |
| MERS         | Middle East Respiratory Syndrome                        |
| NIV          | Non Invasive Ventilation                                |
| PRNT50       | Plaque Reduction Neutralization Test 50 %               |
| RT-PCR       | Reverse Transcription Polymerase Chain Reaction         |
| SAE          | Serious Adverse Event                                   |
| SARS         | Severe Acute Respiratory Syndrome                       |
| SoC          | Standard of Care                                        |
| SARS-CoV-2   | SARS-coronavirus-2                                      |
| SOFA         | Sequential Organ Failure Assessment                     |
| TRALI        | Transfusion-Related Acute Lung Injury                   |
| UK-ICNARC    | United-Kingdom Intensive Care National Audit & Research |

## 6. Ethical and regulatory considerations

- The Principal Investigator at each center will ensure that this study is conducted in agreement with the Declaration of Helsinki as well as the laws and regulations of the country, whichever provides the greatest protection for the patient.
- All study documents (protocol, any protocol amendment, informed consent form and other relevant documents (eg. recruitment advertisements...)) will be submitted to the Ethics Committee for formal approval to conduct the study. The decision of the EC concerning the conduct of the study will be made in writing to the promotor. All correspondence with the IRB/IEC should be retained in the Trial Master File.
- The protocol will be approved by the local Ethics Committee, with the Comité d'Ethique Hospitalo-Facultaire de Liège serving as the central Ethics Committee.
- The protocol will be registered in ClinicalTrial.gov before initiation.
- The study will be conducted in accordance with legal and regulatory requirements (Belgian law of 7 May 2004, Patient rights (August 2002), Private life (RD 2001), HBM (Human Body Material, law of 19 December 2008), RGPD (25 May 2018), as well as the Guidelines for Good Clinical Practice (International Conference on Harmonization), and the last version of Declaration of Helsinki (World Medical Association).

## 7. Objectives

### 7.1. Primary

The principal objective of the CONFIDENT trial is to assess the efficacy of 2 units (400-500mL) of plasma collected in convalescents of COVID-19 infection with a titer greater or equal to 1/320 (plaque reduction neutralization test 50) neutralizing antibodies against SARS-CoV-2 with the standard of care, as compared to standard of care, to reduce the mortality at day 28 after inclusion of the patients with SARS-CoV-2 pneumonia who require mechanical ventilation. In case of shortage of plasma with a titer greater or equal to 1/320 on the moment of patient enrolment, plasma from convalescent donors with a titer of at least 1/80 will be released for transfusion. The standard of care will be made of therapies currently recommended in international guidelines regarding organ failure support and treatment of secondary events. At the present time, no treatment is directed against SARS-CoV-2 or the inflammatory response characteristic of this specific disease. In case of evolution of the guidelines due to new scientific release during the study period, the standard of care will be adapted in the two treatment groups.

### 7.2. Secondary

The secondary objectives are to assess:

- the efficacy of convalescent plasma
  - o to reduce day-90 mortality
  - o to reduce the duration of mechanical ventilation over the 28 days after inclusion,
  - o to reduce the severity of organ failure over the 28 days after inclusion,
  - o to reduce the use of organ support over the 28 days after inclusion
  - o to reduce the viral load, expressed as cycle threshold, over the 28 days after inclusion
  - o to reduce the intensity of the inflammatory response during the 28 days following inclusion.
  - o to reduce the acute care hospital length of stay
  - o to increase the functional, psychological state and quality of life at day 90 and at day 365 after inclusion
  - o to assess the impact of convalescent plasma on sero-conversion against SARS-CoV-2
- the incidence of adverse events related to plasma transfusion
- the incidence of adverse events related to organ support.

